## Abstract

**Introduction:**

Despite the benefits, cardiovascular rehabilitation programs (CRPs) have been related to the appearance of signals and symptoms. Risk stratification protocols are commonly used to identify risks during the physical exercise; however, studies that investigate their efficacy to previse signals and symptoms are inconclusive. Furthermore, clinical, physical, and biochemical parameters have been used as risk markers for the appearance of adverse events, and to investigate their efficacy to previse signals and symptoms during the CRP sessions that could better guide the strategies adopted on these programs.

**Objectives:**

The aim of this study was to evaluate the correlations between risk stratification protocols and clinical, physical, and biochemical parameters with the appearance of signals/symptoms during CRP, as well as to evaluate if modifications on clinical, physical, and biochemical parameters could influence in the appearance of signals/symptoms during CRP.

**Materials and methods:**

The study was prospectively registered at ClinicalTrials.gov (NCT03446742). Forty-four patient participants of a CRP will be evaluated. First, their risk stratification is going to be performed by 2 evaluators and their clinical, physical, and biochemical parameters are going to be measured. Then, the patients are going to be followed during 24 sessions during their CRP routines in order to identify appearance of their signals/symptoms. So, the patients are going to perform their cardiovascular rehabilitation routines for 6 months and then, their clinical, physical, and biochemical parameters are going to be measured again and they are going to be followed during 24 sessions during their CRP routines in order to identify the appearance of their signals/symptoms.

## Introduction

1

Cardiovascular diseases (CVDs) are considered the main cause of death in the world and their appearance is associated with changes^[1–3]^ that directly compromise the quality of life.^[4]^ Therefore, strategies to treat and prevent CVD are fundamental.

Cardiovascular rehabilitation programs (CRPs) are highlighted as an efficient way to prevent and treat CVD, mainly because of its beneficial effects.^[5–8]^ However, during the physical activity practice, a metabolic demand increase happens and promotes changes in the organism,^[9,10]^ which can facilitate the occurrence of signals and symptoms commonly found in CRP.^[11]^ In this context, to investigate factors that could previse the appearance of signals and symptoms during the CRP, would better guide the strategies adopted for its performance.

The literature has shown that clinical, physical, and biochemical parameters, such as heart rate variability (HRV),^[4,12–15]^ cardiorespiratory parameters,^[16–19]^ functional capacity (FC), muscle strength (MS),^[20–23]^ and inflammatory cytokines,^[24,25]^ have been used as a risk marker of mortality, cardiovascular complications, and adverse events on different population, and that some of these parameters are also correlated with specific responses during the physical exercise.^[26–31]^ However, a literature research did not point studies that analyzed whether these parameters could be used as a risk predictor of signals and symptoms during the CRP session. Furthermore, these parameters can directly influence the intensity of these alterations promoted by the exercise and, consequently, be related with the appearance of signals and symptoms.

It is important to highlight that patients submitted to a CRP generally have their risk stratified through different protocols, which allows the practitioner to identify their level of cardiovascular risk.^[32]^ However, some of these protocols efficacy to previse serious complications during the CRP did not obtain significative results.^[33–35]^

Taken together, these data point to some gaps in the literature. How are the risk stratification protocols effective to previse signals and symptoms during the CRP? Can clinical, physical, and biochemical parameters be used to previse signals and symptoms during the CRP? If yes, is it possible to establish a cut-off point for these parameters that can better previse the appearance of signals and symptoms in these programs? Are changes in clinical, physical, or biochemical parameters induced by CRP accompanied by changes in the appearance of signals and symptoms during the CRP?

This study was designed to answer these questions: to evaluate the risk stratification protocols efficacy to previse signals and symptoms during the CRP; to analyze the correlation between clinical, physical, and biochemical parameters, measured at rest, with the presence of signals/symptoms in CRP participants; and to evaluate whether changes in clinical, physical, or biochemical parameters, induced by CRP, will influence the appearance of signals and symptoms during these programs.

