### Sample size

2.2

The sample size was based on rMSSD index^[36]^ because it presents the highest sample number necessary for this study, compared with the other main variables [6 minutes walking test^[37]^ and tumor necrosis factor (TNF)-alpha^[38]^]. A standard deviation of 17 ms, alpha risk of 5%, and beta of 80% was considered for the calculus, which resulted in 44 subjects.

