### Study design

2.4

This study is going to be divided in 3 phases. Initially, all the volunteers are going to have their medical records analyzed, and information about the sample characterization and medical examinations are going to be extracted. Two independent blinded and trained measurers are going to realize the risk stratification of the volunteers, using the protocols described into the literature review of Silva et al.^[39]^ Following this, clinical (cardiorespiratory parameters and autonomic modulation), physical [maximum isometric resistance (MIR), maximum isometric voluntary contraction (MIVC), cardiorespiratory fitness, and physical activity level], and biochemical [interleukin (IL)-6, TNF-alpha, and IL-10] parameters are going to be evaluated by a blinded and trained measurer and the subjects are going to be accompanied during 24 sessions of their CRP routines, to register the appearance of their signals and symptoms.

In the second phase, the volunteers are going to realize their normal CRP routines for 6 months. In the third phase, the clinical, physical, and biochemical parameters, described above, are going to be evaluated by a blinded and trained measurer and the volunteers are going to be accompanied for more 24 sessions of their CRP routines, to register the appearance of their signals and symptoms as well.

The description of the phases and the volunteers that will be included in each one of them are reported at Fig. 1.

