### Data analysis

2.12

The normality of data is going to be analyzed using Shapiro--Wilk test. According to the distribution, the population characteristics will be presented, as mean and standard deviation for parametric distribution and median and interquartile interval for nonparametric distribution.

The relationship between the number of signals and symptoms of the patients and the scale degree of the protocols (1, 2, and 3) is going to be analyzed using Pearson correlation. The concordance degree of each protocol with the number of signals and symptoms are going to be determined using coefficient of intraclass correlation. To determine the efficacy of the risk stratification protocols as soon as clinical, physical, and biochemical parameters to previse signals and symptoms during the CRP, analysis of sensibility and specificity using ROC curve is going to be done. The sensibility, specificity, and predictive value (positive and negative) for the occurrence of events are going to be also registered. If the values of the area on the curve are ≥0.650, it will be considered significative.

To evaluate whether the clinical, physical, and biochemical modifications have influenced in the occurrence of signals and symptoms, the sphericity of the data will be verified by Mauchly test, and if the sphericity be violated, Greenhouse--Geiser correction will be performed. The comparison between the different moments of the clinical (cardiorespiratory parameters and autonomic modulation), physical (maximum isometric endurance, MIVC, cardiorespiratory fitness and physical activity level), and biochemical (IL-6, TNF-alpha, and IL-10) are going to be realized by repeated measures analysis of variance (ANOVA) and the possible differences between the moments will be performed by Bonferroni post-hoc.

The statistical significance difference adopted is going to be fixed in 5% with 95% of confidence interval. The analysis is going to be done on SPSS 15.0 version (SPSS Inc., Chicago, IL).

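### Sensitivity and specificity at cut-offs sought in the same 44 patients, over about 32 parameters, are apparent accuracy and biased upward; report optimism-corrected figures

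*Protocol article*

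**What the plan says.** All references are to the protocol article.

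- **Aim.** Section 1 (Introduction) asks, if the parameters prove usable for prediction, "is it possible to establish a cut-off point for these parameters that can better previse the appearance of signals and symptoms in these programs". It goes on: "This study was designed to answer these questions". The objectives then listed do not repeat the cut-off.
- **Analysis.** Section 2.12 (Data analysis) says of the stratification protocols and the clinical, physical and biochemical parameters that "analysis of sensibility and specificity using ROC curve is going to be done". It adds: "The sensibility, specificity, and predictive value (positive and negative) for the occurrence of events are going to be also registered". The decision rule is: "If the values of the area on the curve are ≥0.650, it will be considered significative".
- **Sample.** The Abstract states: "Forty-four patient participants of a CRP will be evaluated". Section 2.2 (Sample size) bases this on rMSSD: "A standard deviation of 17 ms, alpha risk of 5%, and beta of 80% was considered for the calculus, which resulted in 44 subjects".
- **Second round.** In section 2.4 (Study design) the third phase measures the parameters again, after which "the volunteers are going to be accompanied for more 24 sessions of their CRP routines". The use that section 2.12 states for the repeated parameter measurements is a repeated-measures ANOVA between moments.

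**The concern.** For a continuous marker, sensitivity, specificity and predictive values exist only at a threshold. The article names none in advance, so following the text leads to a threshold taken from the ROC curve of the same 44 patients. The search fits noise as well as signal, so accuracy at the chosen point is overstated on average. Highlighting the best of many markers adds a second layer of selection.

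Section 3 (Final considerations) hopes that resting variables will make programmes safer, partly for patients without recent tests. A cut-off published with inflated sensitivity could give false reassurance in that group.

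**Working it through.** **1. The plan's own figure.** Section 2.2 gives SD 17 ms, alpha 5% and a figure of 80%, which I read as power. It gives no difference to detect, so 44 cannot be reproduced directly. Solving back with two-sided alpha:

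- Paired: delta = (1.960 + 0.842) × 17 / √44 = 7.18 ms.
- Two groups of 22: delta = (1.960 + 0.842) × 17 × √(2/22) = 14.36 ms.

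Either way, the calculation concerns a difference in rMSSD and does not size the ROC analysis.

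**2. Number of parameters.**

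| Source | Parameters | Count |
|---|---|---|
| 2.7 | systolic and diastolic BP, HR, SatO2, respiratory rate, MIP, MEP | 7 |
| 2.7 | PEF, FEV1, FVC, FEV1/FVC | 4 |
| 2.7.3 | RMSSD, SDNN, LF and HF (each in ms² and nu), LF/HF | 7 |
| 2.7.3 | SD1, SD2, SD1/SD2 | 3 |
| 2.8 | MIR, MIVC, 6MWT | 3 |
| 2.8.4 | three activity levels, steps, counts | 5 |
| 2.9 | IL-6, TNF-alpha, IL-10 | 3 |

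The total is 7 + 4 + 7 + 3 + 3 + 5 + 3 = 32, or 40 with the 8 stratification protocols.

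**3. Measure.** J = sensitivity + specificity − 1, which is 0 for a useless marker. For a normal marker with equal variances and true AUC A, the best attainable value is J = 2Φ(d/2) − 1 with d = √2 Φ⁻¹(A). For A = 0.65, d = 0.545 and J = 0.215. For A = 0.75, J = 0.367.

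**4. Simulation at n = 44.** The cut-off maximises J in the sample. *Assumed, because the documents do not give them:* the Youden rule, normal markers, the outcome split and the true AUC. Ranges come from separate runs.

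| Case | Split | Apparent J | True J at the chosen cut-off |
|---|---|---|---|
| One useless marker | 22/22 | 0.24 | 0 |
| One useless marker | 11/33 | 0.28 | 0 |
| Best of 32 useless markers | 22/22 | 0.43–0.44 | 0 |
| Best of 32 useless markers | 11/33 | 0.50 | 0 |
| One marker, true AUC 0.65 | 22/22 | 0.33–0.34 | 0.17–0.19 |
| One marker, true AUC 0.65 | 11/33 | 0.36 | 0.18 |
| One marker, true AUC 0.75 | 22/22 | 0.47 | 0.33 |

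A best-of-32 J of 0.43 corresponds to sensitivity 0.72 and specificity 0.71 from pure noise (0.719 + 0.714 − 1 = 0.433). A pairwise correlation of 0.3 between markers barely changes it (0.427). More uneven splits are worse: 0.46–0.47 at 30/14 and 0.61–0.62 at 38/6.

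**5. The 0.650 rule does not filter this out.** With 32 useless markers, the direction of each chosen from the data and a 22/22 split, at least one reaches AUC 0.650 in 88–95% of simulated studies. About 3 of the 32 are expected to do so.

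**6. Bootstrap correction, with the cut-off search repeated in each resample.**

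- True AUC 0.65: apparent 0.34 becomes 0.21, against a true 0.18. This removes (0.34 − 0.21)/(0.34 − 0.18) = 81% of the optimism.
- Useless marker: apparent 0.24 becomes 0.09, against a true 0. This removes 0.15/0.24 = 63%.

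**7. Phase 3 as a check.** This takes the best of 32 useless markers, a 22/22 split and marker correlation 0.3. Apparent J is about 0.43 and true J is 0. The phase-1 cut-off is applied unchanged in phase 3.

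| Marker correlation between phases | Share keeping outcome status | J seen in phase 3 |
|---|---|---|
| unrelated | unrelated | 0.00 |
| 0.5 | 0.5 | 0.06 |
| 0.8 | 0.5 | 0.10 |
| 0.8 | 0.8 | 0.17 |
| 0.9 | 0.9 | 0.23 |

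With stable patients about half of the false accuracy survives (0.23/0.43 = 53%).

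**The case against.** The best reply is that the article never says it will pick the optimal point on each curve. The cut-off is a conditional question in the Introduction, section 2.12 gives no selection rule, and a condensed article may leave thresholds and internal validation to a fuller document. That is fair as far as it goes: missing validation detail is not the finding, and the Youden rule is my assumption. What remains is what the article does state. It makes the cut-off a study question and registers threshold-dependent accuracy for many continuous markers in one sample, with no threshold fixed beforehand.

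The size is also open to challenge. The 0.44 to 0.50 range applies to the single best of 32 useless markers. For one marker chosen in advance with true AUC 0.75, the optimism is 0.47 − 0.33 = 0.14. This stands: the inflation is strongest for the markers that look best, and a reader should not infer that every marker is overstated to that degree.

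A reader might also infer that phase 3 supplies a free and sufficient validation that the plan ignores. The documents do not support this. Phase 3 follows the same volunteers after six months of the programme, less anyone excluded for attendance under 30% (section 2.1). Chance associations can carry over, as step 7 shows. Nor does section 2.12 confine the ROC analysis to phase 1; it is silent on which phase is used.

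**Conclusion.** The concern holds in this form: as section 2.12 reads, accuracy at cut-offs found in the same 44 patients would be apparent accuracy and biased upward. Under the stated assumptions, sensitivity + specificity − 1 is roughly doubled for a marker with true AUC 0.65. It is about 0.24 to 0.28 for one useless marker and 0.44 to 0.50 for the best of 32. The direction of the bias does not depend on the assumed split or true AUC, but its size does. The article defines no binary event for the ROC, so the actual split is unknown.

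**What to change.** In section 2.12:

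1. Derive cut-offs from phase-1 parameters and phase-1 sessions only.
2. Report bootstrap optimism-corrected AUC, sensitivity and specificity as the main accuracy figures. Repeat the cut-off search in each resample, and also the selection among markers wherever a best marker is highlighted.
3. As a secondary analysis, apply the phase-1 cut-offs unchanged to phase-3 parameters and sessions. Call this a temporal check in the same patients, and state that it can remain optimistic when markers and outcomes are stable.
4. Label every cut-off exploratory until it has been tested in new patients.

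All the data are already planned, so the cost is a little more analysis work. The reported accuracy will be lower. At n = 44 the correction is only partial for useless markers (0.24 falls to 0.09, not to 0), which is why step 4 is needed even after correction.

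### The plan announces a correlation of clinical, physical and biochemical parameters with signs and symptoms, but correlates the symptom count only with the risk stratification protocols

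*Protocol article*

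**What the plan says.** **Aim.** The abstract's Objectives treat the two groups of predictors alike: the study is to "evaluate the correlations between risk stratification protocols and clinical, physical, and biochemical parameters with the appearance of signals/symptoms during CRP". The Introduction repeats the aim for the parameters alone: "to analyze the correlation between clinical, physical, and biochemical parameters, measured at rest, with the presence of signals/symptoms in CRP participants". It also asks, if prediction proves possible, "is it possible to establish a cut-off point for these parameters that can better previse the appearance of signals and symptoms".

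**Outcome.** Section 2.11 (Signals and symptoms identification) records signs and symptoms at each of 24 sessions and counts each one at most once per session. The result is a count per patient.

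**Analysis (section 2.12).** Pearson correlation is given to "The relationship between the number of signals and symptoms of the patients and the scale degree of the protocols". Agreement is also for the protocols: "The concordance degree of each protocol with the number of signals and symptoms are going to be determined using coefficient of intraclass correlation". The parameters enter with the protocols in the next step, where "analysis of sensibility and specificity using ROC curve is going to be done", with sensitivity, specificity and predictive values; an area of 0.650 or more counts as significant. The only other analysis of the parameters is a repeated-measures ANOVA between moments, which contains no symptom variable.

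**The concern.** Two predictor groups share one correlation aim, and the printed analysis gives the count-based method to one of them. This is a mismatch inside the text shown, not a detail left to another document.

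It is more than a matter of wording. A ROC curve needs each patient labelled as event or no event. Two patients with 1 and 20 recorded events can then carry the same label. The Final considerations speak of a high prevalence of signs and symptoms, so a split at any event could leave few event-free patients. At stake is how well a sample of 44 can show a graded relation for the largest group of predictors, and how often it shows one that is not there.

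**Working it through.** **1. Aims against methods**

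| Predictor | Announced | Analysis using the count | Analysis using a yes/no outcome |
|---|---|---|---|
| Risk protocols | correlation, prediction | Pearson, ICC | ROC |
| Parameters | correlation, prediction, cut-off | none | ROC |

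**2. Number of parameters.** From sections 2.7 to 2.9: 11 cardiorespiratory (blood pressure as two), 10 HRV indices, MIVC, MIR and 6-minute walk (3), accelerometer measures (3 intensities, steps, counts: 5), 3 cytokines. 11 + 10 + 3 + 5 + 3 = 32.

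**3. The plan's N.** The 44 subjects rest on an rMSSD standard deviation of 17 ms, 5% alpha and 80% power (printed as beta). The article prints no difference, so 44 cannot be reproduced. It would correspond to a difference of 17 × 2.80 / √44 ≈ 7.2 ms in a paired two-sided comparison. I take 44 as given. For a correlation, the smallest value detectable with 80% power is tanh(2.80 / √41) ≈ 0.41.

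**4. Count model.** None of these inputs is in the documents; all are assumptions. Count ~ negative binomial, mean 6, log-rate slope 0.45 per SD of the parameter, dispersion k with variance μ + μ²/k (24 at k = 2, 42 at k = 1). The chance of no event at the mean is (k/(k + 6))^k: 6% at k = 2, 14% at k = 1. That is about 3 or 6 event-free patients among 44. Each scenario has 4,000 runs (Monte Carlo error below 1 point). Tests are two-sided at 5%; the AUC rule is counted in either direction.

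Power of a 5% test:

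| k | Spearman on count | ROC test, median split | ROC test, any event |
|---|---|---|---|
| 2 | 82% | 67% (loss 15) | 18% (loss 64) |
| 1 | 58% | 43% (loss 15) | 17% (loss 41) |

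The plan's rule, AUC ≥ 0.650 (separate simulation, hence slightly different Spearman figures):

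| k | Spearman on count | AUC rule, median split | AUC rule, any event |
|---|---|---|---|
| 2 | 84% | 78% (loss 6) | 64% (loss 20) |
| 1 | 59% | 55% (loss 4) | 46% (loss 13) |

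With slope 0, Spearman rejects in about 5% of runs. The AUC rule is met in about 9% at a median split and 28 to 45% at any event (a repeat gave 26 to 43%). At slope 0.3 the detection gap largely closes.

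**5. A second model.** Bivariate normal, n = 44, correlation ρ also assumed:

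| ρ | Spearman | 5% ROC test, 50 / 80 / 90% events | AUC rule, 50 / 80 / 90% events |
|---|---|---|---|
| 0 | 5% | 5 / 5 / 4% | 9 / 18 / 34% |
| 0.3 | 46–47% | 33 / 26 / 17% | 44 / 51 / 58% |
| 0.4 | 73% | 54 / 43 / 28% | 65 / 68 / 72% |
| 0.5 | 92% | 76 / 63 / 41% | 84 / 85 / 83% |

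The direction is the same. A 5% test of the split outcome always detects less than Spearman. The AUC rule detects somewhat less at ρ = 0.4 and 0.5, and is level or higher at ρ = 0.3, where it gains hits by accepting false ones.

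**6. False positives over 32 parameters with no association.** 5% test: 32 × 0.05 = 1.6. AUC rule at a median split: 32 × 0.09 ≈ 2.9. At any event: 32 × 0.28 ≈ 9 to 32 × 0.45 ≈ 14. If a direction were fixed in advance for each parameter, symmetry would halve the AUC-rule figures.

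**The case against.** The strongest reply is that the aim already has its analysis. The Introduction speaks of the presence of symptoms, which is a yes/no notion, and asks for a cut-off. ROC answers both, and the AUC is itself a rank measure of association with presence. On this view, correlation is a loose word for relationship in a condensed article. This stands in part: ROC belongs in the plan, and a reader who infers that the aim has no analysis at all goes too far. It does not explain why the protocols, under the same aim, get a count-based correlation as well as ROC. Nor does it use the graded outcome that section 2.11 collects.

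Three further inferences are tempting and not supported:

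- *The plan states that it dichotomises the count.* It names no split. The need for one follows from ROC; the median and any-event splits above are mine.
- *The plan loses 15 to 65 power points.* Those figures belong to a 5% test. The plan judges the AUC against 0.650, and under that rule the loss is smaller and disappears for weak associations.
- *The count is discarded.* It is used for the protocols; it is unused only for the parameters.

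It is also fair to say that about 30 extra tests at 5% bring their own false positives, about 1.6 with no association. That bears on how the added analysis is read, and applies with more force to the AUC rule.

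**Conclusion.** The point holds as a mismatch between aim and analysis. A correlation with signs and symptoms is announced for the parameters, the count-based analysis is planned only for the protocols, and ROC covers the aim in part.

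The cost of leaving it so depends on inputs that the documents do not give. At a slope of 0.45 and k of 1 to 2, Spearman keeps its 5% level and still detects about 4 to 6 points more than the plan's rule at a median split, and 13 to 20 points more at any event. At weaker associations the gain is mainly in error control. What does not depend on the assumed effect size is that a fixed AUC threshold has no set error rate with 44 patients: it is met by chance more often the more uneven the split. The change is worth making because it is cheap; nothing here invalidates the ROC analysis for finding cut-offs.

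**What to change.** In section 2.12, add one sentence: for each clinical, physical and biochemical parameter, report a Spearman correlation with 95% confidence interval against signs and symptoms per attended session, or a negative-binomial model of the count with log sessions attended as offset. The denominator matters because section 2.1 excludes only patients below 30% attendance, so observed sessions may differ; if everyone is observed for 24 attended sessions, it changes nothing. Report this alongside ROC, which stays as the analysis for the cut-off question.

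Rewording the aim to match ROC would remove the mismatch, but would leave the count unused for the parameters.

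**Cost.** No new data and no change to procedures. There is more output, and about 30 further tests that should be labelled exploratory or adjusted for multiplicity.

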## Materials and methods

2

This is a longitudinal observational study of a cohort, registered prospectively on ClinicalTrials.gov (NCT03446742). It going to be developed with a convenience sample of patients regularly attending a CRP based on exercise.

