### Eligibility criteria

2.1

Subjects of both genders, with clinical diagnosis of CVD and/or cardiovascular risk factor, able to realize all the evaluations proposed and in accordance to the study procedures are going to be included. Patients with less than 30% of attendance during the period of the protocol are going to be excluded.

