### Sample characterization

2.5

For the sample characterization, the volunteers’ medical records are going to be analyzed in order to identify information about their age, gender, clinical diagnoses, cardiovascular risk factors, and associated pathologies (musculoskeletal, neurological, pulmonary, and/or metabolic disfunction).

For the volunteers’ risk stratification according to the protocols selected in this study, their clinical history and the results of their last laboratory and complementary examinations related to the cardiovascular system are going to be extracted from their medical records.

For the clinical history, information about the number of cardiorespiratory arrests, hospital days, and complications during the hospital days or after procedures are going to be considered. For the laboratory tests, blood glucose, triglycerides, total cholesterol, high-density lipoprotein (HDL)-cholesterol, and low-density lipoprotein (LDL)-cholesterol are going to be considered. For the complementary examinations, cardiovascular examinations, such as exercise stress test, echocardiogram, Holter, catheterization, myocardial scintigraph, electrocardiogram, and coronary angiotomography are going to be considered.

We are also going to measure the height in orthostatic position with a stadiometer (Sanny, Personal Caprice, Brazil) and body mass with a digital balance (Balmak, Premium, Bk–200Fa, Brazil), in order to calculate the body mass index (BMI).^[40]^

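### Objective 3 speaks of parameter changes induced by CRP, but one cohort already attending the program, with no pre-program measurement and no comparison group, can only show change observed during continued participation.

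*Protocol article*

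**What the plan says.** All references are to the protocol article.

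- **Objective (Introduction).** The study is to evaluate whether "changes in clinical, physical, or biochemical parameters, induced by CRP, will influence the appearance of signals and symptoms". The last of the research questions just before it attributes the changes to the program in the same way.
- **Objective (Abstract).** Here the aim is only to see whether modifications of the parameters could influence signals and symptoms. The program is not named as their cause.
- **Design (Materials and methods).** "This is a longitudinal observational study of a cohort", drawn as a "convenience sample of patients regularly attending a CRP based on exercise". The Abstract agrees: "Forty-four patient participants of a CRP will be evaluated".
- **Eligibility (2.1).** "Subjects of both genders, with clinical diagnosis of CVD and/or cardiovascular risk factor, able to realize all the evaluations proposed" may enter. Nothing restricts entry to new participants or limits earlier attendance. Patients below 30% attendance are excluded.
- **Phases (2.4).** After the first measurements and 24 observed sessions, "In the second phase, the volunteers are going to realize their normal CRP routines for 6 months". The parameters are then measured again and "the volunteers are going to be accompanied for more 24 sessions of their CRP routines".
- **Analysis (2.12).** The parameters are compared between moments, within this cohort, by repeated measures ANOVA with Bonferroni post-hoc tests.

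**The concern.** To say that the program induced a change, one needs a value from before the program, or a group in whom time passes without it, and preferably both. The text describes neither. The first measurement falls at an unspecified point in each patient's attendance, and the exposure between the two measurements is the one patients already had.

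Two things are at stake. First, any before-after difference would be reported as an effect of the program, although other causes acting over the same months would look identical. Second, patients may enter with very different amounts of earlier training, so part of any response may already have happened before the first measurement. Without time in program, a reader could not tell a small change in a trained group from a program that does nothing.

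**Working it through.** **1. Objective against design.**

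| Needed to credit change to the program | What the text provides |
|---|---|
| A measurement before the program starts | First measurement in patients already attending (Materials and methods; Abstract) |
| New entrants, or known prior exposure | No limit on prior time (2.1); prior time not given |
| A change of exposure between measurements | Usual routine continued (2.4) |
| A comparison group | One cohort; none described |
| An analysis isolating the program's contribution | Comparison of moments within the cohort (2.12) |

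Sampling and timing are fixed by the design. A separate analysis plan could not create a baseline or a comparator.

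**2. Time between the measurements.** The program runs 3 times a week (2.10). At full attendance 24 / 3 = 8 weeks, about 1.8 months. Adding the 6 months of phase 2 gives about 8 months. If the 24 sessions are counted as attended sessions, a patient at the 30% attendance limit needs 24 / 0.30 / 3 = 26.7 weeks, about 6 months, so the interval approaches 12 months. This leaves room for drug changes, disease progression and a different season.

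**3. The plan's own sample size.** Section 2.2 gives SD 17 ms, alpha 5%, 80% (printed as beta, read here as power) and 44 subjects, but no difference to detect. The 44 therefore cannot be reproduced forward. Solved backward, with 17 ms assumed to be the SD of the within-patient change and a two-sided test:

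delta = (1.960 + 0.842) × 17 / √44 = 7.18 ms.

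**4. Illustration: a shift unrelated to the program.** With two moments, repeated measures ANOVA is equivalent to a paired t-test. Its critical value on 43 degrees of freedom is 2.017. The standard error of the mean change is 17 / √44 = 2.56 ms, so an observed mean change beyond 2.017 × 2.56 = 5.17 ms is significant whatever its cause. From the noncentral t with noncentrality shift × √44 / SD, the probability of a significant result when the program adds nothing is:

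| True shift | SD of change 13.2 ms | 17 ms | 20.1 ms |
|---|---|---|---|
| 2 ms | 17% | 12% | 10% |
| 4 ms | 50% | 33% | 25% |
| 6 ms | 84% | 63% | 49% |

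The outer columns treat 17 ms as the SD at one moment and use SD of change = 17 × √(2(1 − r)), with correlation r between moments of 0.7 and 0.3. At r = 0.5 the result is 17 ms again. The shifts and correlations are assumptions.

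**5. Illustration: attenuation.** If patients already in the program show only a fraction of the 7.18 ms, the power of the paired t-test with 44 patients and a change SD of 17 ms is 78% at the full change, 54% at three quarters, 28% at half and 11% at a quarter. The documents do not say which fraction applies.

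**The case against.** The strongest reply is that the real target is the link between parameter change and symptom change, whatever caused the former. The Abstract states the aim without attributing change to the program, the Introduction's own question asks whether the two kinds of change go together, and section 2.12 plans no test of a program effect. This stands as far as it goes: the association can still be studied, and the correction is mostly one of wording. It does not rescue the Introduction, which attributes the changes to CRP twice and so claims more than the Abstract and more than the design can deliver.

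A reader might infer several stronger points. The documents do not support them:

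- *That little or no change is to be expected.* Prior time in the program is not reported, and recent entrants could still change. Figure 1, which describes the volunteers in each phase, is not available here. Attenuation is possible, but its size cannot be derived. An assumed training curve with an assumed time constant would only return those assumptions.
- *That a null for objective 3 would mean the design left almost no change to study.* Relating change to change needs variation in change between patients, not a non-zero mean. A mix of new and long-standing attenders may increase that variation.
- *That prior exposure confounds the other two objectives.* They concern prediction and correlation and make no causal claim. Differing prior exposure is there a matter of case mix.
- *That the start date and drug use are not collected.* Section 2.5 lists "identify information about their age, gender, clinical diagnoses, cardiovascular risk factors, and associated pathologies" and further history, and section 2.11 sets up a patient record that includes medicines. A condensed article that does not list a start date does not show that it is not recorded.

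**Conclusion.** The concern holds as a mismatch between the third objective and the design. As described, the study can report change during continued participation and its association with symptoms, but it cannot credit the change to CRP. This follows from the stated sampling, eligibility and phases, and depends on no disputed figure.

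The numbers only show that the risk is not trivial: a 4 to 6 ms shift in rMSSD from other causes would be declared significant in roughly 33% to 63% of such studies if the change SD is 17 ms, and 25% to 84% across the SDs tried. The size of any attenuation is unknown. The other two objectives are not affected. The correction is worth making because it changes what the trial may conclude, and it costs little.

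**What to change.** 1. In the Introduction, replace *induced by CRP* with *observed during continued CRP participation* in both places, which brings the objective into line with the Abstract. State the interval as at least about 8 months between measurements at full attendance, and report the actual interval.
2. Limit the conclusion to an association between parameter change and symptom change.
3. Take each patient's CRP start date from program records. Enter time in program at phase 1 as a continuous covariate in the change analysis, centred so that the effect of moment refers to a patient with average prior time. Splitting 44 patients at an arbitrary cut-off would risk a very small or empty stratum.
4. Use the medicines record of section 2.11 to describe drug changes between the phases, confirming that it is updated at phase 3.

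The cost is a changed phrase, one date per patient and one covariate with 44 patients, together with a weaker causal claim. The covariate helps to interpret the size of the change. It does not replace a pre-program baseline or a comparison group, so the causal wording should not return once it is added.
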